## Abstract

**Background:**

Due to increasing interest from acne patients concerned about the side effects associated with conventional therapies, complementary and alternative medicine (CAM) has been suggested as a new therapeutic modality for acne vulgaris. Herbal medicine is one of these CAM treatments. *Cheongsangbangpoong-tang* (CBT) is a common herbal formula used in patients with acne vulgaris in the clinical practice of Korean Medicine (KM). However, despite the common use of CBT in clinical practice, the current level of evidence is insufficient to support an inhibitory effect of CBT on inflammatory acne lesions and facial heat. Therefore, this study was designed to assess the inhibitory effect of CBT on both inflammatory acne lesions and facial heat.

**Methods/design:**

A randomized, double-blind, parallel-group, and placebo-controlled trial will be conducted. Fifty-six participants with acne vulgaris will be randomized into one of two groups: the CBT or placebo groups. After randomization, participants will be prescribed either CBT or placebo three times a day at a dose of 5 g after meals for 8 weeks. The following outcome measurements will be used in the examination of subjects: the mean percentage change and the count change of the inflammatory and non-inflammatory acne lesions, the temperature of facial points on digital infrared thermal imaging (DITI), serum cortisol, serum dehydroepiandrosterone-sulfate (DHEA-S), visual analogue scale (VAS), investigator global assessment (IGA), and severity score on the Korean Acne Grading System (KAGS) from baseline to the end of the trial.

**Discussion:**

This trial will provide evidence regarding the inhibitory effect of CBT on inflammatory acne lesions and facial heat. The findings of this trial may have important implications for the more widespread use of CBT for the treatment of acne vulgaris.

**Trial registration:**

The trial is registered with the Clinical Research Information Service (CRiS), Republic of Korea: KCT0001468.

## Background

Acne is a multifactorial inflammatory skin disease of the pilosebaceous unit [1]. With respect to pattern identification, which is defined as “the process of overall analysis of clinical data to determine the location, cause and nature of a patient’s disease” [2], acne is deeply relevant to the ‘*Heat*’ pattern [3, 4]. Patients diagnosed as suffering from a ‘*Heat*’ pattern, such as the ‘*Wind-Heat*’ or ‘*Dampness-Heat*’ patterns, in their dermatologic disease have characteristics similar to the inflammatory state [5].

In Korea, *Cheongsangbangpoong-tang* (CBT) has been approved by the Korea Food and Drug Administration as a prescription for clinical use in patients with acne, and is most frequently used by Korean Medicine (KM) clinicians in patients with acne vulgaris. CBT was first mentioned in ‘*Wanbinghuichun’* as a novel herbal therapeutic formula. It cleans the *upper energizer pathogenic heat*, which is considered the major pathogenic cause of acne in Korean traditional medicine, and treats the sores and furuncles on the head and face [6]. However, until now, no well-designed and randomized clinical trial supporting this classic substance has been performed.

We hypothesized that CBT inhibits acne inflammatory lesions and facial heat mainly displayed by patients identified as suffering from a ‘*Heat*’ pattern. The purpose of this research is to evaluate the inhibitory effects of CBT, an herbal formula, on both inflammatory acne lesions and facial heat in patients with acne vulgaris.

## Method/design

### Aim of the study

The primary objective of the present trial is to investigate the inhibitory effects of the herbal formula CBT on both inflammatory acne lesions and facial heat in patients with acne vulgaris.

The primary null hypothesis is as follows: CBT treatment is superior to placebo treatment in its inhibitory effect on the mean percent change in inflammatory acne lesions between baseline and the end of the trial.

### Design

This study is a randomized, placebo-controlled, parallel-group, double-blind and single-center trial. This trial is registered with the Clinical Research Information Service (CRiS), Republic of Korea: KCT0001468. The study will be sequentially conducted as follows: enrollment after screening via inclusion and exclusion criteria, randomization, a treatment period of 8 weeks, and assessment.

In addition, the protocol will be conducted in accordance with the Declaration of Helsinki and the Good Clinical Practice Guidelines [7]. All investigators are appropriately qualified to conduct and supervise the trial. All patients will provide written informed consent prior to study entry. The flow chart of this study is shown in Fig. 1.

**Fig. 1 Fig1:**
[figure not shown]
Flow chart of the study

### Ethics

The study protocol and written informed consent were approved by the Institutional Review Board (IRB) of the Kyung Hee University Korean Medicine Hospital (KOMCIRB-150213-HR-006). Each participant will be provided with information regarding the study protocol. Written informed consent will be obtained from each patient. The privacy of all participants will be protected. Personal medical records will be reviewed by investigators, who will promise to keep the content confidential. Data anonymity will be used in the process of data management. Finally, the data of all subjects will be kept in the document storage room of Kyung Hee Korean Medicine-Clinical Trial Center (K-CTC).

### Participants and eligibility

#### Inclusion criteria

Patients with acne vulgaris aged over 19 years, who have more than 10 inflammatory acne lesions on their face (from the jawline margin to the front margin of hairline), and who agree to use only the intervention in this study for acne vulgaris treatment during this trial period are eligible to participate in this trial.

#### Exclusion criteria

We will exclude patients with laboratory findings in the following ranges: aspartate transaminase (AST) ≥ 60 IU/L, alanine transaminase (ALT) ≥ 60 IU/L, and creatinine > 1.2 mg/dl. Participants will be ineligible if they have undergone Western medical treatment or traditional medical treatment or taken oral contraceptives/antibiotics for acne within 2 weeks prior to recruitment or are pregnant, lactating, or planning to become pregnant during the study. Participants will also be excluded if they are not willing to comply with this study protocol. During the 8 weeks after enrollment in this trial, no concomitant acne therapy will be permitted.

### Recruitment

Participants will be recruited via an internet advertisement posted on the website of the Kyung Hee Medical Center and via posted flyers. A total of fifty-six patients will be recruited in this trial.

### Randomization and allocation concealment

Using a stratified block randomization method, 56 eligible patients will be randomly allocated to the CBT or placebo groups in a 1:1 ratio in blocks of 4. Random numbers will be generated by a computerized random-number generator using the block-randomization method of a software program (R 3.2.2) for sequence generation by an independent statistician. The randomization lists will be concealed in a lightproof sealed envelope. The sealed envelopes will be kept by the independent statistician of the study. Participants, investigators and outcome assessors will be blinded to the treatment allocation throughout the course of the study.

### Blinding and code breaking

Drugs (CBT and placebo) have been coded, providing masking to the treatment assignment to ensure double blinding. Patients, clinicians, outcome assessors, and investigators are unaware of treatment group assignments or block size. If a participant has a serious adverse event and immediate cessation of trial medication is required, the blinding code will be broken.

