### Intervention

#### CBT and placebo groups

CBT granule is approved by the Korea Food and Drug Administration as a prescription for use in clinical practice for patients with acne. The components of CBT are presented in Table 1. Each of the CBT crude materials was extracted with 500 mL of hot water for 48-72 hours. The extracts were filtered, concentrated, lyophilized, and stored at -60 °C. The yield of CBT dried extract was approximately 15.8 % (w/w, dry weight 1.5 g). The other excipients (corn starch and lactose CARB) were added to this dried CBT extract. CBT granules were purchased from the Han Kook Sin Yak Pharm. Co., which is equipped with a Korean good manufacturing practice (KGMP) facility. A voucher specimen (# KCTC 001502) was deposited at K-CTC.

**Table 1 Tab1:** Components of *Cheongsangbangpoong-tang* (CBT) granules (5 g / dose)

Scientific name	Amount (g)
*Schizonepeta tenuifolia*	0.5
*Coptis japonica Makino*	0.5
*Mentha arvensis var. piperascens*	0.5
*Ponciri Fructus Immaturus*	0.5
*Glycyrrhiza uralensis FISCH*	0.5
*Gardenia augusta*	1.0
*Cnidium officinale*	1.0
*Scutellaria baicalensis*	1.0
*Forsythia koreana*	1.0
*Angelica dahurica*	1.0
*Platycodon grandiflorum*	1.0
*Ledebouriella seseloides*	1.0
*Corn starch*	1.2
*Lactose hydrate*	2.3
Total	5.0

Participants assigned to the placebo group will receive a placebo prescription instead of the herbal formula CBT throughout the 8-week post-randomization period. The placebo will not have any clinical or pharmacological effects. The placebo is almost identical to the test drug in appearance, smell and taste. This placebo preparation will be produced and purchased from the Jeonnam Biofood Technology Center, which is equipped with a Korean good manufacturing practice (KGMP) facility. The placebo granules, designed to match the CBT granules, to be used in this trial are identically sized granules filled with lactose powder (95.2 %), dextrin (2.94 %), herbal incense (0.7 %) and coloring (food coloring such as brown food coloring) (1.16 %), without any markings or active ingredients.

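### The protocol says staff do not know the block size, yet it prints a single fixed size of 4, so the claimed masking of block size is not supported

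*Protocol article*

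**What the plan says.** Two adjoining sections of the protocol article deal with the block size.

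- **Randomization and allocation concealment:** the method is stratified block randomisation, with patients "randomly allocated to the CBT or placebo groups in a 1:1 ratio in blocks of 4". One size is given, with no mention of variation. An independent statistician generates the list in R, and "The sealed envelopes will be kept by the independent statistician of the study".
- **Blinding and code breaking:** the article says that "investigators are unaware of treatment group assignments or block size", and the same sentence covers patients, clinicians and outcome assessors. The drugs are coded. After a serious adverse event that requires immediate cessation of trial medication, "the blinding code will be broken".

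Three other places bear on the point. CBT and placebo groups states: "The placebo is almost identical to the test drug in appearance, smell and taste". Standard operation procedures for quality assurance says that a written protocol will be provided, without describing its contents. Trial status gives the start of recruitment as October 19, 2015, in the future tense.

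**The concern.** The authors list the block size next to treatment assignment as something that patients, clinicians, assessors and investigators do not know, and then publish it. Both statements cannot hold for anyone who reads this text. The article mentions no restricted randomisation document and no staff version without the size.

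The block size is worth masking because a short fixed block lets someone who learns one allocation infer something about its neighbours. The document itself allows two ways of learning one: a code break, and recognition of a placebo that is not claimed to be a perfect match. The Discussion says that a herbal placebo perceived as identical is extremely difficult to prepare. Lesion counts from photographs and the IGA are human judgements, so inferred allocations could in principle influence them.

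**Working it through.** The plan gives no figure to reproduce, so the check measures what knowledge of the block size could add.

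**Inputs from the document:** block size 4, ratio 1:1, 56 patients, hence 56/4 = 14 complete blocks if strata are ignored. The article does not give the strata. The sums below assume one list.

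**1. Block size known, no allocation known.** By symmetry each patient is equally likely to be in either arm, so the correct-guess rate is 50%. There is no gain.

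**2. Block size and boundaries known, one code break.** Three places remain in the block, two of them in the opposite arm. Each of the other three patients is therefore in the opposite arm with probability 2/3 = 67%. Over the other 55 patients the average correct-guess rate is (3 × 2/3 + 52 × 1/2)/55 = 28/55 = 50.9%.

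**3. Upper bound: block size, boundaries and every earlier allocation known.** There are 6 balanced sequences of length 4.

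| Position in block | Probability the allocation is certain | Probability of a correct best guess |
|---|---|---|
| 1 | 0 | 1/2 |
| 2 | 0 | 2/3 |
| 3 | 1/3 (first two in the same arm) | 1/3 × 1 + 2/3 × 1/2 = 2/3 |
| 4 | 1 | 1 |

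- Share certain: (0 + 0 + 1/3 + 1)/4 = 33.3%.
- Average correct guess: (1/2 + 2/3 + 2/3 + 1)/4 = 70.8%.

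**4. Same upper bound with varying blocks.** Assume sizes 4 and 6 drawn at random with equal probability, and an observer who knows the scheme and every earlier allocation but not the individual sizes. Simulating lists of 56 and updating the probability of each possible block state after every allocation gives about 5.5% certain and a correct-guess rate of about 69.0%.

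| | Fixed blocks of 4 | Unknown random blocks of 4 and 6 |
|---|---|---|
| Allocations certain | 33.3% | about 5.5% |
| Average correct guess | 70.8% | about 69.0% |

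Varying the sizes therefore removes most of the certainty and almost none of the average predictability.

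**The case against.** The strongest reply is that concealment never depended on the block size. The list is held by an independent statistician in sealed envelopes, the drugs are coded, and packages are uniform with the same labels. A reader might infer from the contradiction that allocation concealment or double blinding is broken. The document does not support that: with treatment masked, step 1 gives 50%. This part of the reply stands in full.

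Four further replies also limit the point.

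- **The claim may be true at the site.** This is a condensed article, and the staff version of the protocol may omit the size. That is possible, so the claim can be called unsupported but not shown to be untrue. Nor does the article establish that it was published before recruitment began. It gives only a planned start date.
- **The upper bound is remote.** It needs every earlier allocation in order. The one planned unmasking event is a code break after a serious adverse event, and step 2 shows how little one such break adds.
- **The placebo route is thin.** Participants, not assessors, taste the granules, and a check of blinding success is planned. A participant who recognises the product is already unblinded. Block size matters only if staff learn of it and carry the inference to others.
- **Stratification weakens inference.** With more than one stratum, members of a block need not be consecutive enrolees.

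It is also fair to say that a fixed block of 4 is defensible in a masked single-centre trial of this size. What survives is that the protocol claims a masking property and discloses the masked value without saying how the two are reconciled.

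**Conclusion.** The point holds in a narrow form. The stated unawareness of block size is not supported by the protocol's own text. No failure of allocation concealment or double blinding is shown, and no bias in the primary outcome is demonstrated. The expected bias is small, because it requires allocations to become known first: one code break moves the average correct guess over the other patients only from 50% to 50.9%.

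The 33% and 70.8% are upper bounds. They assume a single list, known block boundaries and full knowledge of earlier allocations. The comparison with about 5.5% and 69.0% assumes equal use of sizes 4 and 6, unknown to the observer. This is a minor point, worth acting on because the change is cheap.

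**What to change.** **Before the first randomisation:** have the independent statistician generate the stratified list with randomly varying block sizes, for example 4 and 6. Keep the sizes in a restricted randomisation document and remove them from every document that staff see. The statement under Blinding and code breaking is then supported.

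**Cost:** a few lines of R and a wording change. The drug codes must follow the new list. An incomplete block of 6 can leave a list unbalanced by up to 3, against up to 2 for an incomplete block of 4, and such imbalances can add up over strata.

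**If the list is already fixed:** delete the reference to block size from the sentence under Blinding and code breaking, so that it claims unawareness of treatment assignment only and agrees with the randomisation section. This is purely editorial. It removes the contradiction but leaves predictability unchanged.

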### Intervention

#### CBT and placebo groups

CBT granule is approved by the Korea Food and Drug Administration as a prescription for use in clinical practice for patients with acne. The components of CBT are presented in Table 1. Each of the CBT crude materials was extracted with 500 mL of hot water for 48-72 hours. The extracts were filtered, concentrated, lyophilized, and stored at -60 °C. The yield of CBT dried extract was approximately 15.8 % (w/w, dry weight 1.5 g). The other excipients (corn starch and lactose CARB) were added to this dried CBT extract. CBT granules were purchased from the Han Kook Sin Yak Pharm. Co., which is equipped with a Korean good manufacturing practice (KGMP) facility. A voucher specimen (# KCTC 001502) was deposited at K-CTC.

**Table 1 Tab1:** Components of *Cheongsangbangpoong-tang* (CBT) granules (5 g / dose)

Scientific name	Amount (g)
*Schizonepeta tenuifolia*	0.5
*Coptis japonica Makino*	0.5
*Mentha arvensis var. piperascens*	0.5
*Ponciri Fructus Immaturus*	0.5
*Glycyrrhiza uralensis FISCH*	0.5
*Gardenia augusta*	1.0
*Cnidium officinale*	1.0
*Scutellaria baicalensis*	1.0
*Forsythia koreana*	1.0
*Angelica dahurica*	1.0
*Platycodon grandiflorum*	1.0
*Ledebouriella seseloides*	1.0
*Corn starch*	1.2
*Lactose hydrate*	2.3
Total	5.0

Participants assigned to the placebo group will receive a placebo prescription instead of the herbal formula CBT throughout the 8-week post-randomization period. The placebo will not have any clinical or pharmacological effects. The placebo is almost identical to the test drug in appearance, smell and taste. This placebo preparation will be produced and purchased from the Jeonnam Biofood Technology Center, which is equipped with a Korean good manufacturing practice (KGMP) facility. The placebo granules, designed to match the CBT granules, to be used in this trial are identically sized granules filled with lactose powder (95.2 %), dextrin (2.94 %), herbal incense (0.7 %) and coloring (food coloring such as brown food coloring) (1.16 %), without any markings or active ingredients.

All drugs are concealed in uniform packages with the same labels in the Jeonnam Biofood Technology Center and each package contains a 28-day supply. Patients in the CBT or placebo groups will take each packaged granule containing either 5 g CBT or 5 g placebo as a single dose. All drugs will be dissolved in 200 ml warm water and will be taken orally after each meal 3 times daily for 8 weeks. During the study, patients will be visited three times by the investigators. We will establish the window for visits as ±3 days. Details of the study procedures are shown in Table 2.

**Table 2 Tab2:** Detailed study procedures

Items	Screening/run-in period	Visit 1 (baseline)	Visit 2	Visit 4 (endpoint)
Week of the trial	-1	0	4	8
Demographic information-taking	+			
Informed consent form	+			
General medical history-taking	+			
Photographing the patient’s face Count of inflammatory/non-inflammatory lesions	+	+	+	+
Blood tests (AST, ALT, creatinine, serum cortisol, serum DHEA-S)	+			+
Urine pregnancy test	+		+	+
Digital infrared thermal imaging		+	+	+
Randomization & allocation	+			
Distribution of treatment or placebo		+	+	
Visual analogue scale		+	+	+
Investigator Global Assessments		+	+	+
Korean Acne Grading System		+	+	+
Pattern identification for acne	+			
Monitoring adverse events			+	+
Compliance check			+	+
Blinding check				+

### Outcome measures

#### Primary outcome

Primary outcome will be presented as the mean percentage change of inflammatory lesion counts from baseline to the end of the trial [8, 9].

### Secondary outcomes

Secondary outcomes will evaluate the mean percentage change of non-inflammatory lesions and the total of both inflammatory and non-inflammatory lesions, the differences in temperatures of the DITI points on the face, Visual Analogue Scale (VAS) [score 0 (no symptoms) to 100 (severe symptoms)], and the Investigator Global Assessment scale for Facial Acne Vulgaris (IGA; after evaluation from score 0 (clear) to 4 (severe)) [10] from baseline to the end of the trial (at 8 weeks) between CBT treatment and the placebo control groups. Serum cortisol and dehydroepiandrosterone-sulfate (DHEA-S) will be assessed using clinical laboratory tests at weeks 0 (baseline) and 8 (end of the trial).

VAS and IGA will be checked every session from baseline (just before randomization) through the 8 weeks after randomization. A Lumix DMC-LX2 digital camera (Panasonic, Osaka, Japan) will be used to photograph the front and both sides of each patients face, so that the inflammatory and non-inflammatory lesions can be counted independently at weeks 0 (baseline), 4 and 8 (end of the trial) by a clinical specialist who has been in clinical practice for more 5 years. We will consider black and white head comedones to be non-inflammatory lesions and the inflammatory papules, pustules and cysts to be inflammatory lesions.

Correlations between the inflammatory lesion count and the temperatures of the DITI points at baseline, 4 weeks, and 8 weeks, and the frequency of abnormal liver and kidney function during this trial will also be secondary outcomes. Additionally, we will analyze the correlation between the temperatures of the DITI points and the severity of the Korean Acne Grading System (KAGS) at baseline and the end of the trial (at 8 weeks). Finally, we will analyze the success rate of blinding between the actual treatment and the perceived treatment allocations.

### Withdrawal, dropout, discontinuation and compliance

Participants will be allowed to withdraw at any time during this clinical trial. Participants who wish to withdraw will be offered the option to cease trial intervention, but continue the visits for outcome measurement. Participants who withdraw will be followed to investigate the reason for withdrawal. Participants may be advised to discontinue this trial if there is a serious intervention-related adverse event or if the participant is noncompliant with the study procedure. CBT or placebo remaining after each session will be quantified in order to measure and enhance medication compliance. Participants whose compliance with CBT or placebo is ≤ 80 % of the total will be considered to have dropped out.

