### Adverse events and safety monitoring

All unexpected adverse events related to CBT or the placebo intervention will be reported to the investigator by participants and written on the individual case report form by the investigator. Safety will be assessed by the reporting of clinical laboratory tests and adverse events. Clinical laboratory tests, including AST / ALT and creatinine, will be performed at screening and week 8 (the end of the trial). Each participant will be monitored for adverse events (pain at acne lesions or other sites, nausea/vomiting, fatigue, allergic reaction, and any adverse events related to intervention) after each visit.

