### Statistical methods

#### Statistical analysis plan

Statistical analyses will be conducted on both intension-to-treat (ITT) and per-protocol (PP) bases, with a 95 % confidence interval using SPSS version 12.0 for Windows. Based on the ITT population, the primary outcome and safety outcome will be tested. Secondary outcome will be analyzed on both the ITT and PP populations. The ITT analysis will consider all randomized participants with at least one measurable outcome value during the study. Missing values from drop-out participants will be imputed by the last observation carried forward (LOCF) method. Data will be displayed as the mean ± standard deviation (SD) for continuous data or n (%) for categorical data.

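### Continued outcome visits are offered only to participants who choose to withdraw, not to those advised to leave for a serious related adverse event or noncompliance, so week-8 data can be lost avoidably

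*Protocol article*

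**What the plan says.** All references are to the protocol article. Its section on withdrawal, dropout, discontinuation and compliance describes three situations.

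- **Voluntary withdrawal.** "Participants who wish to withdraw will be offered the option to cease trial intervention, but continue the visits for outcome measurement". Stopping the drug and leaving the study are kept apart.
- **Advised discontinuation.** Others may instead be "advised to discontinue this trial if there is a serious intervention-related adverse event or if the participant is noncompliant with the study procedure". What is discontinued is the trial, and continued visits are not mentioned.
- **Low dose-taking.** A participant who takes 80% or less "of the total will be considered to have dropped out".

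Table 2 places the "Compliance check" at weeks 4 and 8. Its row "Blood tests (AST, ALT, creatinine, serum cortisol, serum DHEA-S" is marked only at screening and week 8, and the adverse-events section agrees that the safety tests "will be performed at screening and week 8 (the end of the trial".

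On analysis, the plan states "Based on the ITT population, the primary outcome and safety outcome will be tested" and "Missing values from drop-out participants will be imputed by the last observation carried forward (LOCF) method".

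**The concern.** Both triggers for advised discontinuation arise after randomization and can depend on treatment; a serious event judged related to the intervention is the plainest case. If these participants leave the trial rather than just the drug, their week-8 values are missing for a reason that may differ between arms. LOCF then puts a week-4 or baseline efficacy value where an observed week-8 value could have stood.

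Safety is the sharper issue. Someone who leaves before week 8 has no scheduled laboratory result after screening. Yet the frequency of abnormal liver and kidney function is a named secondary outcome, and AST, ALT and creatinine are to be compared between groups at week 8. The participants most likely to show harm could be those without the test.

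**Working it through.** **1. Does any other text extend the offer?** The offer of continued visits is tied to participants who wish to withdraw, and the advice sentence carries none. The section on blinding and code breaking covers a serious adverse event that requires the medication to be stopped, but it provides only for breaking the code and says nothing about later visits. The remaining follow-up sentence concerns the reason for withdrawal. No section extends the offer to advised exits.

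**2. How many participants?** The Sample size section gives 28 per arm and a 20% dropout allowance:

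- 28 × 0.20 = 5.6 per arm.
- The share of dropouts that would be advised exits is not given. Taking 0 to 100% as the range gives 0 to 5.6 per arm. The upper end requires every planned dropout to be an advised exit.

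The 28 is used here only as the planned arm size. It does not follow from the stated effect: 17.3/44.45 = 0.39 needs about 104 per arm for 80% power, two-sided, before dropout. That is a separate matter and does not bear on this point.

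**3. What happens to the efficacy values?** Lesion counts are taken at weeks 0, 4 and 8. A participant who leaves after week 4 has the week-4 value carried forward. One who leaves before week 4 has at most a baseline value to carry, which means a change of zero. Only missing values are imputed, so an attended week-8 visit removes the imputation for that participant without altering the analysis section.

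**4. What happens to the laboratory values?** For a participant who left, the week-8 value is either absent or the carried screening value. The exclusion criteria force that screening value to have AST and ALT below 60 IU/L and creatinine at most 1.2 mg/dl. Per participant, with 28 as the denominator:

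- New abnormality at week 8 missed: −1/28 = −3.6 percentage points.
- Same classification either way: 0.
- Abnormal screening value carried although week 8 would be normal: +1/28 = +3.6 points. This can occur only if the cut-off for abnormality lies below the exclusion limits. The article gives no cut-off; an assumed example is a cut-off of 40 IU/L and a screening value of 50.

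Unless an unscheduled test is done, a new week-8 abnormality in such a participant goes unseen.

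**5. Can noncompliance reach someone who is still attending?** If the total means all planned doses:

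- 3 per day × 56 days = 168 doses; 80% of 168 = 134.4.
- At most 134 taken means at least 168 − 134 = 34 missed.
- By week 4, 3 × 28 = 84 doses are due. Missing 34 of them (34/84, about 40%) already settles the dropout rule.

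The week-4 compliance check could therefore identify such a participant with the week-8 visit still to come. This matters only if dose-taking counts as part of the study procedure, which the text leaves open.

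**The case against.** The advice is discretionary, so the participant still decides. Someone who accepts it could be said to wish to withdraw and so receive the existing offer. The section on code breaking describes the serious-event pathway as stopping medication, which tells against reading the other sentence as a deliberate end to follow-up. The article mentions a written protocol and standard operating procedures that are not shown, and these may settle visit handling. The noncompliance route needs two steps that the text does not link: that missed doses count as noncompliance with procedure, and that the investigator then gives the advice. The number affected is unknown, adverse events are still recorded and compared, and no effect on the primary outcome is shown. Finally, the remedy adds off-treatment data by the plan's own advice.

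Much of this stands as a limit on size. The loss is permitted, not required; the numbers are probably small; the noncompliance route is conditional. It does not remove the point. The overlap with voluntary withdrawal is a possible reading that the text does not state, and the section itself distinguishes stopping the intervention from leaving the trial. This is more than missing detail, because the printed rule names leaving the trial as the step. No later analysis plan can recover a visit that did not take place. As to the remedy, advice to leave the trial already entails stopping the drug, so the grounds for stopping are not widened. The same paragraph already accepts off-treatment data from voluntary withdrawals.

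**Conclusion.** The point holds. As written, the section permits avoidable loss of week-8 efficacy data and of the only scheduled post-baseline AST, ALT and creatinine in participants whose exit may be related to treatment. The range is 0 to 5.6 of 28 per arm, assuming the plan's 20% dropout and an unknown share of advised exits. Each such participant can shift an arm's frequency of abnormal function by −3.6 to +3.6 percentage points, the positive end depending on a cut-off that is not given. The size and direction of any bias in the primary outcome cannot be derived from the document, and none is claimed. The change is worth making because it is cheap; the planned analysis is not invalid without it.

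**What to change.** In the section on withdrawal, dropout, discontinuation and compliance:

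- Make trial medication, not the trial, the thing a participant may be advised to discontinue.
- State that everyone who stops medication, for whatever reason, is offered the remaining scheduled visits, including lesion counts, thermal imaging, IGA, VAS and the week-8 blood tests, unless consent to follow-up is withdrawn.

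This costs one or two sentences. The visits and tests are already in Table 2, and the grounds for stopping medication stay as they are. The downside is that some off-treatment data enter the ITT analysis. Little is gained where noncompliance means not attending.
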